## Abstract

**Background:**

Inflammation has been implicated in driving the morbidity associated with subarachnoid hemorrhage (SAH). Despite understanding the important role of inflammation in morbidity following SAH, there is no current effective way to modulate this deleterious response. There is a critical need for a novel approach to immunomodulation that can be safely, rapidly, and effectively deployed in SAH patients. Vagus nerve stimulation (VNS) provides a non-pharmacologic approach to immunomodulation, with prior studies demonstrating VNS can reduce systemic inflammatory markers, and VNS has had early success treating inflammatory conditions such as arthritis, sepsis, and inflammatory bowel diseases. The aim of the Non-invasive Auricular Vagus nerve stimulation for Subarachnoid Hemorrhage (NAVSaH) trial is to translate the use of non-invasive transcutaneous auricular VNS (taVNS) to spontaneous SAH, with our central hypothesis being that implementing taVNS in the acute period following spontaneous SAH attenuates the expected inflammatory response to hemorrhage and curtails morbidity associated with inflammatory-mediated clinical endpoints.

**Materials and methods:**

The overall objectives for the NAHSaH trial are to 1) Define the impact that taVNS has on SAH-induced inflammatory markers in the plasma and cerebrospinal fluid (CSF), 2) Determine whether taVNS following SAH reduces radiographic vasospasm, and 3) Determine whether taVNS following SAH reduces chronic hydrocephalus. Following presentation to a single enrollment site, enrolled SAH patients are randomly assigned twice daily treatment with either taVNS or sham stimulation for the duration of their intensive care unit stay. Blood and CSF are drawn before initiation of treatment sessions, and then every three days during a patient’s hospital stay. Primary endpoints include change in the inflammatory cytokine TNF-α in plasma and cerebrospinal fluid between day 1 and day 13, rate of radiographic vasospasm, and rate of requirement for long-term CSF diversion via a ventricular shunt. Secondary outcomes include exploratory analyses of a panel of additional cytokines, number and type of hospitalized acquired infections, duration of external ventricular drain in days, interventions required for vasospasm, continuous physiology data before, during, and after treatment sessions, hospital length of stay, intensive care unit length of stay, and modified Rankin Scale score (mRS) at admission, discharge, and each at follow-up appointment for up to two years following SAH.

**Discussion:**

Inflammation plays a central role in morbidity following SAH. This NAVSaH trial is innovative because it diverges from the pharmacologic status quo by harnessing a novel non-invasive neuromodulatory approach and its known anti-inflammatory effects to alter the pathophysiology of SAH. The investigation of a new, effective, and rapidly deployable intervention in SAH offers a new route to improve outcomes following SAH.

**Trial registration:**

Clinical Trials Registered, NCT04557618. Registered on September 21, 2020, and the first patient was enrolled on January 4, 2021.

## Introduction

### Background and rationale

Intracranial aneurysms are common, with 3–5% of all adults harboring at least one. The resulting subarachnoid hemorrhage (SAH) from ruptured aneurysms accounts for 5–10% of all strokes worldwide, culminating in a total of 600,000 new cases per year [1]. SAH is a major driver of mortality and morbidity, with 10–25% of patients dying following SAH and an additional 30% of patients suffering permanent disability [2]. While the immediate sequelae of SAH can include risk for re-rupture, elevated intracranial pressure, and acute hydrocephalus, secondary injury is a major driver of morbidity as mediated by early brain injury, cerebral vasospasm, delayed cortical ischemia, and chronic hydrocephalus [3]. Targeting the post-hemorrhage period with the goal of reducing these secondary sequelae from SAH is an important mechanism for improving outcomes in SAH patients.

There is growing evidence that systemic and local inflammation may promote aneurysm formation and rupture as well as lead to poorer outcomes following aneurysmal rupture. Following SAH, blood within the subarachnoid space triggers both local, as measured by inflammatory markers in the cerebrospinal fluid (CSF), and systemic inflammatory responses, as measured by inflammatory markers in the blood. Prior work has identified increased cytokines including IL-1β, IL-4, IL-8, IL-10, IL-18, and IL-33, following SAH in animal [4–7] and human [8–13] studies. Key drivers of SAH-induced inflammation are the cytokines IL-6 and TNF-α. Studies in canine and rabbit models of SAH demonstrate increased rates of vasospasm correlated with expression of IL-6 in the basilar artery [6] and CSF [14], respectively. Work performed in humans reveals elevated IL-6 in the blood [11] and CSF [9, 11, 15–17] following SAH. In several studies, elevated IL-6 in the CSF was significantly correlated with development of vasospasm [9, 16], delayed cortical ischemia [17], chronic hydrocephalus [18, 19], and poorer overall outcome [9, 11] following SAH. Similarly, studies in rodent [20] and rabbit [21] models of SAH found increased TNF-α was associated with vasospasm. In humans, elevated TNF-α in the blood [22, 23] and CSF [8, 9, 24, 25] have been demonstrated following SAH. Elevated TNF-α has been associated with vasospasm [8, 9, 24], hydrocephalus [8], and poor outcome [8, 22].

Numerous anti-inflammatory interventions have been trialed in humans to better understand, and eventually target, inflammatory pathways to improve outcomes after SAH [26–29]. In smaller enrollment studies, there was promise of outcome improvement with Cyclosporine A [30, 31] and steroids like methylprednisolone [32, 33], hydrocortisone [34], and dexamethasone [35]. Other medications demonstrated no impact on overall outcomes, like Clazosentan [36, 37], Cilostazol [38], and IL-1 antagonists [39, 40]. In several meta-analysis studies looking at groups larger than 1000 patients, Simvastatin [41], Aspirin, non-steroidal anti-inflammatory medications, and thienopyrindines [42] all demonstrated no improvement in outcomes. In summary, while some pathway-targeted pharmacological approaches have led to changes in secondary outcomes of vasospasm and delayed cerebral ischemia in clinical trials [37, 38], these approaches have failed to produce an effective intervention that reliably improves outcomes in SAH patients. Thus, there is an urgent need to find a novel approach to more globally and meaningfully reduce inflammation in SAH to reduce patient morbidity.

Vagus nerve stimulation (VNS) has been studied as a novel method of reducing inflammation. Substantial work has demonstrated that products of infection or injury activate sensory neurons traveling to the brainstem in the vagus nerve [43, 44]. The arrival of these incoming signals generates action potentials that travel from the brainstem to the spleen and other organs. This culminates in T cell release of acetylcholine, which interacts with α7 nicotinic acetylcholine receptors (α7 nAChR) on immunocompetent cells to inhibit cytokine release in macrophages [45]. This neural-immunomodulatory circuit, referred to as the “cholinergic anti-inflammatory pathway”, presents opportunities for developing novel therapeutic strategies to treat inflammatory diseases. It has been successfully implemented in models of inflammatory conditions like induced neuroinflammation [46], cerebral ischemia/reperfusion [47], rheumatoid arthritis [48], sepsis [49], and inflammatory bowel diseases [50, 51] or colitis [52]. Harnessing its anti-inflammatory effects, VNS has been used in a mouse model of cerebral aneurysms and SAH [53]. In this study, pre-treatment with VNS not only reduced the rupture rate of intracranial aneurysms, but also reduced the grade of hemorrhage if rupture occurred and improved survival and outcome after SAH [53]. There has not been any published work implementing VNS following SAH in humans.

Historically, VNS was performed exclusively by surgical cervical neck dissection and placement of a cuff electrode directly around the nerve within the carotid sheath. Alternatively, VNS can be accomplished non-invasively by stimulating the auricular branch of the vagus nerve as it courses through the external ear, obviating the morbidity of a surgical procedure and allowing rapid deployment of the intervention in critically ill patients. The external ear is an ideal target for non-invasive stimulation of the vagus nerve, where the auricular branch travels in the concha of the ear [54]. This transcutaneous auricular approach has demonstrated good efficacy, with minimal morbidity [54, 55].

Taken together, there is substantial evidence that VNS is an emerging tool to mitigate inflammation, but there is a dearth of understanding on its effects on SAH in humans.

### Objectives

Our long-term goal is to translate the use of non-invasive transcutaneous auricular VNS (taVNS) to reduce morbidity and improve outcomes in patients following spontaneous SAH. The overall objectives for the NAVSaH trial in pursuit of achieving this goal are to (i) demonstrate the impact taVNS has on inflammatory markers in the blood and CSF in patients following SAH, and (ii) determine if taVNS reduces the incidence of inflammation-mediated sequelae of SAH by performing a prospective, randomized controlled trial. Our central hypothesis is that implementing taVNS in the acute period following spontaneous SAH will attenuate the expected inflammatory response to hemorrhage and will curtail morbidity associated with inflammatory-mediated clinical endpoints (i.e., vasospasm & hydrocephalus). By pursuing this project, we expect to demonstrate the important role that neuromodulation can play in SAH. More specifically, we expect this work will create the foundation of knowledge for advancing non-invasive taVNS to enable further research to translate this as an established clinical intervention in the future.

## Materials and methods

### Trial design

NAVSaH is a prospective, triple-blinded (patient, care team, and outcomes assessor), randomized-control trial to assess superiority of intervention with vagus nerve stimulation following spontaneous subarachnoid hemorrhage compared to standard of care with respect to inflammatory markers in the blood and CSF, rate of radiographic vasospasm, and rate of development of chronic hydrocephalus. Treatment and sham assignments are made with a 1:1 allocation. Figs 1 and 2 represents an overview of the trial design. This protocol manuscript was written in accordance with the Standard Protocol Items: Recommendations for Interventional Trials (SPIRIT) guidelines [56] and the Consolidated Standards of Reporting Trials (CONSORT) statement [57].

**Fig 1 pone.0301154.g001:**
[figure not shown]
SPIRIT schedule of enrollment, interventions, and assessments.

**Fig 2 pone.0301154.g002:**
[figure not shown]
Timeline for enrollment and participation in the NAVSaH clinical trial by participants. Cerebrospinal fluid (CSF).

### Methods: Participants, interventions and outcomes

The Washington University institutional review board reviewed and approved this study. Written informed consent was obtained for all participants.

#### Study setting

The NAVSaH trial is being conducted at a single center, a tertiary care academic hospital center, Barnes Jewish Hospital/Washington University in St. Louis (St. Louis, MO, USA).

#### Eligibility criteria

Participants include all individuals who present with a spontaneous subarachnoid hemorrhage, aged >18 years old. Exclusion criteria includes traumatic etiology for hemorrhage, negative vascular imaging for aneurysm (CT angiogram or cerebral angiogram), ongoing cancer therapy, ongoing use of an immunomodulating or suppressive medication, sustained bradycardia on arrival with a heart rate < 50 beats per minute for > 5 minutes, implanted pacemaker or other electrical device, current pregnancy, or a positive test for the Covid-19 virus.

**Who will take informed consent?** Patients provide written consent for themselves when able. For patients who are unable to provide consent given cognitive impairment from their subarachnoid hemorrhage, then a legally authorized representative can provide written informed consent in conjunction with patient assent (whenever possible). The patient or legally authorized representative are informed about the objectives of the study as well as potential risks and benefits of participation. Documentation of consent is kept in paper format and maintained in a locked and secure storage box by trial staff. Consent is obtained by either a physician member of the research team, or an appropriately trained research coordinator. In all situations, the team member seeking informed consent is not involved in the medical care of the enrollee, to prevent actual or implied bias or compulsion for trial participation.

#### Additional consent provisions for collection and use of participant data and biological specimens

There are no additional consent provisions for specific ancillary studies, however, there is an optional provision in the consent form to allow for use of data collected for future related studies.

#### Interventions

*Explanation for the choice of comparators*. Both arms of the NAVSaH trial will receive standard of care for management of subarachnoid hemorrhage, not limited to intensive care monitoring, treatment of a ruptured aneurysm via endovascular or surgical means as dictated by the physician team, cerebrospinal fluid diversion when considered medically indicated, and repeated imaging studies as deemed necessary by the physician team. Treatment with non-invasive vagus nerve stimulation has been implemented in many other studies, and has a demonstrated safety profile when implemented previously following acute ischemic or hemorrhagic stroke [58]. Sham stimulation, which is delivered as a comparator, involves the placement of ear clips without electrical stimulation has no perceived positive or negative effect on clinical outcome, or foreseeable risk for adverse effects.

*Intervention description*. Enrolled participants are randomized to one of two study arms and receive either 1) twice daily non-invasive auricular vagus nerve stimulation to the left ear, or 2) sham stimulation involving placement of the ear clips without applied electrical current. Treatment is applied twice daily, similar to other studies applying vagus nerve stimulation to drive reduction in inflammation [59–61]. The electrodes are placed on the left ear, consistent with the typical left-sided cervical placement of invasive vagus nerve stimulators [62], although no evidence indicates laterality in cardiac effects in non-invasive stimulation. An enrolled patient will begin with either taVNS or sham stimulation twice daily during their stay in the intensive care unit while continuous heart rate/rhythm, blood pressure, intracranial pressure, and oxygenation monitoring is in place. Each day, there is one session each morning (between 05:00–10:00) and one each evening (between 16:00–21:00). The initial treatment session occurs during the first treatment block time after informed consent is complete. All patients are fitted with a portable TENS (transcutaneous electrical nerve stimulation) unit connected to two ear clips, applied to the left ear during treatment periods. For VNS treatment, these ear clips are placed along the concha of the ear (Fig 3), with positioning optimized to target the auricular branch of the vagus nerve [61]. Stimulation parameters were selected based on prior studies that sought to maximize vagus somatosensory evoked potentials while avoiding perception of pain [63, 64]. Stimulation parameters will be 20 minutes duration, frequency of 20 Hz, 250μs pulse width, and an intensity of 0.4mA. Sham treatments will involve no electrical current. Treatment sessions with either taVNS or Sham stimulation will end after transfer out of the intensive care unit.

**Fig 3 pone.0301154.g003:**
[figure not shown]
Target for auricular vagus nerve stimulation. Vagus nerve stimulation is administered by placing the stimulating electrodes along the concha of the ear, where the innervation of the auricular branch of the vagus nerve runs.

*Criteria for discontinuing or modifying allocated interventions*. The study treatment will be discontinued if a participant meets any of the following criteria: if irritation or redness at the stimulation site occurs, evidence of induced clinically significant changes in heart rate or rhythm, or by participant or legally authorized representative request. In these cases, the treatment sessions will cease, but blood and cerebrospinal fluid draws and recording of clinical outcomes will continue unless by request by the patient or legally authorized representative request.

*Strategies to improve adherence to interventions*. All treatment sessions occur while the enrolled patient is admitted to the hospital, and in the intensive care unit. Therefore, we anticipate few barriers to adherence with the intervention.

*Relevant concomitant care permitted or prohibited during the trial*. All medications, procedures, or interventions recommended by the medical team to manage an enrolled patient’s subarachnoid hemorrhage will be permitted. The patient will not be permitted to receive any intervention that is associated with a separate clinical trial.

*Provisions for post-trial care*. There is no anticipated harm and no planned compensation for trial participation. All post-trial care will follow the typical follow-up for patients discharged after subarachnoid hemorrhage (including follow-up imaging or physician office visits). No additional imaging, laboratory studies, or hospital visits are otherwise required due to trial participation alone.

#### Outcomes

The NAVSaH trial’s evaluated end points include: 1) Defining the impact that taVNS has on the SAH-induced inflammatory markers in the plasma and cerebrospinal fluid (CSF), 2) Determining if taVNS following SAH reduces angiographic vasospasm 3) Determining if taVNS following SAH reduces chronic hydrocephalus.

For assessment of the impact taVNS has on inflammatory makers, blood and CSF is collected prior to the initial treatment session as a baseline, and then every three days during the patient’s inpatient hospital stay (CSF collected only when an external ventricular drain is in place). The primary inflammatory marker assessed is TNF-α, although a panel of 13 cytokines is analyzed in an exploratory fashion (IL-1β, IL-2, IL-4, IL-5, IL-6, IL-8, IL-10, IL-12, IL-13, IL-17, TNF-α, GM-CSF, and IFN-γ). Differences regarding the local and systemic inflammatory cytokine TNF-α reduction from baseline to day 13 post-treatment will primarily be examined through the interaction of time and treatment effects, with additional exploratory analyses performed for other days.

To assess angiographic vasospasm, serial vascular imaging studies will be evaluated. In addition to initial diagnostic imaging, patients will undergo a repeat computed tomography or catheter angiogram seven

days after admission, per our hospital’s standard protocol. Additionally, further vascular imaging will be performed if there is clinical concern per the intensive care or neurosurgical teams for clinical vasospasm or stroke. For both planned and indicated imaging sessions, each vascular imaging study will be reviewed by a trained neurointerventionalist blinded to treatment arm, who will measure and quantify the imaging as it relates to vasospasm as none, mild (< 25% stenosis), moderate (25%–50% stenosis), or severe (> 50% stenosis) narrowing of at least one major intracranial artery, as previously described [65, 66].

To evaluate the rate of chronic hydrocephalus, the primary outcome assessed will be binary (placement of ventricular shunt, versus no shunt placement).

The trial’s secondary end points include: patient demographics (gender, ethnicity, and age), number and type of hospitalized acquired infections, duration of external ventricular drain in days, interventions required for vasospasm (blood pressure augmentation, intraarterial medications, intrathecal medications, endovascular intervention with angioplasty), continuous physiology data (heart rate, blood pressure, respiratory rate, intracranial pressure) before, during, and after treatment sessions, hospital length of stay, intensive care unit length of stay, and modified Rankin Scale score (mRS) at admission, discharge, and each at follow-up appointment for up to two years following SAH.

#### Participant timeline

The schematic overview of the NAVSaH trial is shown in Fig 2. Study start-up began in July 2020, including protocol development and single institutional review board approval. Trial enrollment began in January 2021, and it is anticipated that enrollment will continue for approximately 4 years from that date. Participants are enrolled in an acute care setting when they present with a spontaneous SAH, with enrollment occurring within 24 hours of arrival to the hospital. Intervention with taVNS or Sham stimulation occurs twice daily while the patient is in the intensive care unit, and discontinues on transfer to lower level of care from ICU. A mRS is assessed at time of hospital admission, at time of discharge, and at all follow-up appointments with the Neurosurgery clinic or Neuroangiography team in the two years following admission by an assessor blinded to treatment arm. Follow-up with the Neurosurgical and Neuroangiography teams follows standard of care, and no additional follow-up appointments are scheduled strictly for the NAVSaH trial.

#### Sample size

Goal enrollment for the pilot NAVSaH trial is 50 patients, based on power calculations to detect significant differences in inflammatory cytokines, radiographic vasospasm, and chronic hydrocephalus.

Under a 2-by-2 repeated measures design consisting of two groups of patients, each measured at two time points, our goal is to compare the change across time in the taVNS group to the change across time in the Sham group. Based upon previous work from Koopman et al. [67], we assume our study will observe 1.1 standardized inflammatory cytokines mean change difference between the two groups. Using a two-sided, two-sample t-test, assuming both time points have equal variance and there is a weak correlation (i.e., 0.15) between measurement pairs, a sample size of 25 in each group achieves at least 80% power to detect a standardized difference of 1.1 in mean changes, with a significance level (alpha) of 0.05 [68].

Based upon our preliminary data, we assume this study will observe 25% and 55% severe vasospasm in the taVNS and Sham groups, respectively. Under a design with 2 repeated measurements (i.e., 2 raters), assuming a compound symmetry covariance structure with a Rho of 0.2, at a significance level (alpha) of 0.05, a sample size of 25 in each group achieves at least 80% power when the null proportion is 0.55, and the alternative proportion is 0.25 [69–71].

As previously described, LV et al. [8] studied the relationship between cytokine levels and clinical endpoints in SAH, including hydrocephalus. From their outcomes, we predict a needed enrollment of approximately 50 to detect these endpoints. From our own preliminary data, with an incidence of chronic hydrocephalus 0% in treated patients and 28.6% in control (despite grade of hemorrhage), alpha = 0.05 and power = 0.80, the projected sample size to capture that change is approximately 44 patients.

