#### Statistical methods

*Statistical methods for primary and secondary outcomes*. The primary outcome of Aim 1 is quantified continuous measures of the plasma and CSF TNF-α collected at two time points, baseline (before treatment) and day 13 after treatment. The taVNS impact on SAH inflammatory markers will be examined via a linear mixed model, where time (i.e., 0- and 13-days post-treatment), treatment (i.e., taVNS vs. Sham), and time-treatment interaction are the fixed effects, and the dependency of measurements clustered within each individual patient will be accounted for via the random effects. Group differences regarding the local and systemic inflammatory cytokines reduction from baseline to day 13 post-treatment will be examined through the interaction of time and treatment effects. Model assumptions will be inspected, and remedy will be applied if necessary. Secondary outcomes involve exploratory analyses of the remainder of the inflammatory markers collected from plasma and CSF.

The primary outcome of Aim 2 is the highest severity of vasospasm (binary, moderate/severe vs. non moderate/severe) as assessed by measurements performed by a Neurointerventionalist. A mixed effect logistic regression model will be used to examine the taVNS and Sham group difference regarding the severity of vasospasm. A generalized estimating equation (GEE) approach will be used to estimate the model parameters assuming a compound symmetry covariance structure, given there might be a possible unknown correlation between observed outcomes within the same patient. For other secondary clinical metrics related to vasospasm, to detect treatment group differences, based upon the distribution of data, independent t-tests or Wilcoxon–Mann–Whitney tests will be performed for continuous variables, and Chi-square tests or Fisher exact tests will be performed for categorical variables.

The primary outcome of Aim 3 is binary (i.e., shunt vs. non-shunt) and the secondary outcome of Aim 3 is continuous (i.e., the duration of external ventricular drainage). To detect the treatment group difference, a 2x2 contingency table and Chi-square test will be used for the binary outcome, and an independent t-test will be used for the continuous outcome.

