*Methods for additional analyses (e*.*g*. *subgroup analyses)*. To evaluate for effect of grade of hemorrhage (high grade with a Hunt and Hess Score ≥3, versus low grade), the interaction between assigned treatment and the subgroup factor in a linear model will be tested (significance level of P<0.017). The model will include a main effect for treatment, subgroup factor, and an interaction between subgroup and treatment. Secondary outcomes will also be assessed in similar models.

*Methods in analysis to handle protocol non-adherence and any statistical methods to handle missing data*. High levels of missing data for the outcomes of interest are not expected because these are readily available, documented in medical records as part of the standard of medical care for SAH, and are ascertained during the patient’s primary hospital admission. Should there be high rates of participant attrition in the trial, baseline characteristics and available information on the hospital course will be reviewed and compared to participants who do not withdraw from participation to assess for any differences in those who withdraw and those who do not.

*Plans to give access to the full protocol*, *participant level-data and statistical code*. A dataset with group-level, de-identified clinical data and participant-level de-identified laboratory data in accordance with the Health Insurance Portability and Accountability Act (HIPAA), as well as statistical code used for analyses and will be made available upon reasonable request. The team will comply with the clinical trial information dissemination expectations of the NIH policy and FDA/DHHS Final Rule to register and submit summary results at ClinicalTrials.gov. Consistent with the terms and conditions of NIH funding, we will ensure the submission and updating of registration and results information for this clinical trial in the timeframes established by the Final Rule.

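### The 80% power stated for TNF-α change assumes baseline/day-13 pairs from nearly all patients, which the drain-dependent sampling rule gives no reason to expect for CSF

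*Protocol article*

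**What the plan says.** The Abstract and the Statistical methods section make TNF-α in both plasma and CSF, at baseline and day 13, the primary outcome of Aim 1. The Sample size section sets the total: "Goal enrollment for the pilot NAVSaH trial is 50 patients". For the cytokine endpoint it takes two groups, each measured at two time points, and states "we assume our study will observe 1.1 standardized inflammatory cytokines mean change difference between the two groups". The method is given as "Using a two-sided, two-sample t-test, assuming both time points have equal variance and there is a weak correlation (i.e., 0.15) between measurement pairs", and the result is that "a sample size of 25 in each group achieves at least 80% power to detect a standardized difference of 1.1 in mean changes". No compartment is named and no allowance is made for missing samples.

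The Outcomes section schedules blood and CSF before the first session and every three days during the inpatient stay, with the limit "CSF collected only when an external ventricular drain is in place". The Interventions section has CSF diversion used on medical indication. The Eligibility criteria do not require a drain. Drain duration is listed among the secondary end points and is the secondary outcome of Aim 3.

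The primary model is a linear mixed model "where time (i.e., 0- and 13-days post-treatment), treatment (i.e., taVNS vs. Sham), and time-treatment interaction are the fixed effects". Other sampling days are left to exploratory analysis. On missing data the protocol says: "High levels of missing data for the outcomes of interest are not expected because these are readily available, documented in medical records".

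**The concern.** The power statement uses every enrolled patient as a complete pair. For CSF, that would require all 50 patients to have a drain at baseline and still at day 13. Nothing in the protocol supports this, and its own collection rule makes it unlikely.

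The missing-data premise does not fit either. TNF-α is a study assay on samples drawn for the study, not a value already in the chart, and it cannot be measured in CSF from a patient without a drain.

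Two things are at stake for a primary endpoint:
- A null CSF result could be read as coming from an adequately powered comparison when it did not.
- Having a day-13 CSF sample is a post-randomisation event tied to how long the drain stays in. The trial hypothesises that treatment affects hydrocephalus and analyses drain duration as an outcome. A CSF difference at day 13 may therefore compare selected patients rather than the randomised groups.

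**Working it through.** **Inputs (Sample size section):** 25 per group, standardized difference 1.1, ρ = 0.15, equal variances, two-sided α = 0.05, t-test on change. The number of CSF pairs is not in the protocol, so 15, 12 and 8 per group below are assumptions.

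**Step 1: reproduce the stated figure.** The protocol does not say which SD standardizes 1.1.

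- Reading A, single-time-point SD: SD of change = σ√(2(1 − 0.15)) = 1.304σ, so d = 1.1/1.304 = 0.844. With 25 per group the noncentrality is 0.844 × √(25/2) = 2.98 on 48 df, and power is 83.2%.
- Reading B, SD of the change: d = 1.1, and power is 96.8%.

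Both satisfy at least 80%. Reading A is the one that uses ρ and needs a sample size close to 25, so it is the more likely intention.

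**Step 2: pairs needed for 80%.** Reading A needs 24 per group (81.6%; 23 gives 79.9%), a margin of one pair per group. Reading B needs 15.

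**Step 3: t-test on change with fewer complete pairs.**

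| Pairs per group | Reading A | Reading B |
|---|---|---|
| 25 | 83.2% | 96.8% |
| 15 | 60.7% | 82.8% |
| 12 | 50.6% | 73.1% |
| 8 | 34.9% | 53.5% |

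**Step 4: the planned mixed model.** It also uses patients with a baseline sample only. With n complete pairs among N patients with a baseline sample, the variance of the mean change per group is σ²[(1 − ρ²)/n + (1 − ρ)²/N].

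For n = 15 and N = 25: 0.9775/15 + 0.7225/25 = 0.0652 + 0.0289 = 0.0941. The SE of the group difference is √(2 × 0.0941) = 0.434, and power (normal approximation, Reading A) is Φ(1.1/0.434 − 1.96), about 71.8%.

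| Complete pairs + baseline only | Mixed model | Complete pairs, same approximation |
|---|---|---|
| 15 + 10 | 71.8% | 63.7% |
| 12 + 13 | 64.9% | 54.2% |
| 8 + 17 | 51.6% | 39.3% |

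The normal approximation runs slightly high (84.7% against 83.2% at 25 pairs), so these rows should be compared with each other and not with Step 3. The gain requires all 25 per group to have a drain at baseline. A patient who never has a drain adds nothing to the CSF analysis.

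**Step 5: adding the day 4, 7 and 10 samples.** Take patients without day 13 as sampled through day 7, with the same correlation between all pairs of visits. At ρ = 0.15, power for the day-13 contrast moves from 71.8% to 72.1% (15 + 10) and from 58.9% to 59.5% (10 + 15). At ρ = 0.5 it moves from 88.8% to 90.4% and from 76.1% to 79.8%.

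**The case against.** The strongest reply has four parts. The calculation is correct as stated. Under Reading B, 80% survives down to 15 pairs per group. The planned analysis is a mixed model, not a complete-pair t-test, so the lowest figures overstate the loss. And this is a self-described pilot in a condensed article, where missing-data modelling can be left to an analysis plan.

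Most of this is fair and limits the point. It does not remove it. Even Reading B needs a number of CSF pairs that the protocol never states, the mixed model helps only through patients with a baseline drain, and the chart-data premise is wrong for this endpoint in the article itself.

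Four stronger readings are tempting, and the documents do not support them:

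- **That the power calculation is a mistake.** It reproduces for complete pairs.
- **That plasma is underpowered.** The background section speaks of SAH "with 10–25% of patients dying following SAH". If that removed pairs, 22 to 19 per group would remain, with 78% to 72% power under Reading A. But this is general background mortality with no time window, not deaths before day 13 among consented inpatients. It is illustrative only.
- **That a patient sampled through day 10 is wasted, or that using days 4 to 10 would restore power.** The baseline value enters the mixed model, the other days are kept for exploratory analysis, and Step 5 shows under one point gained at the protocol's ρ. Averaging over post-baseline days is a different estimand and still depends on who has a drain.
- **That the CSF result is biased by a known amount or in a known direction.** The protocol gives no drain durations and no correlation between TNF-α and drain retention.

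**Conclusion.** The point stands in a limited form. Applied to CSF, the 80% statement rests on complete sampling that the collection rule does not provide. Under the likelier reading of 1.1, even the mixed model falls short at each assumed number of pairs, and a t-test on change falls further. Under the other reading, 15 pairs would suffice but 12 or 8 would not. How far power falls cannot be settled from the document, because the share of patients with both CSF samples is not given. For plasma the statement is right if pairs are complete, with little slack under Reading A. Possible selection of the CSF comparison is a separate matter that a larger sample would not cure. Its direction and size are unknown.

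**What to change.** 1. Limit the 80% statement to complete baseline/day-13 pairs, which in practice means plasma, and note the margin of one pair per group.
2. State whether 1.1 is in single-time-point or change SDs.
3. Give a separate CSF power at the expected number of patients with a drain at baseline and at day 13, with the source of that number.
4. Correct the missing-data text for cytokines: these are study assays, and CSF is unavailable without a drain.
5. Report the CSF result as restricted to patients with a drain, not as a fully randomised comparison.

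A repeated-measures model on all scheduled samples is optional. If an average over post-baseline days were chosen for CSF, it should be declared as a change of primary estimand that leaves the selection in place.

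Items 1 to 5 are changes of wording plus one short calculation, with no new samples or visits. The cost is a lower stated power for CSF and a more cautious claim from it. The changes should be made before any unblinded analysis.
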